## Methods/Design

### Trial objectives and endpoints

The primary hypothesis of the MIND-DIA trial is that CBT is significantly and clinically more effective than TAU in terms of improvement of health related quality of life (HRQoL) at a one-year follow-up. Therefore, HRQoL (mental component) is analysed as the primary outcome parameter of the present trial.

The secondary hypotheses comprise the assumptions that CBT offers a specific advantage and is significantly more effective than SH, as demonstrated by a significantly greater improvement in HRQoL compared with SH groups at the one-year follow-up. Furthermore, it is surmised that at the one-year follow-up CBT will be found to be significantly more effective than TAU in terms of reduction of depressive symptoms and prevention of moderate/severe major depression, improvement of glycaemic control (HbA1c), prevention of mortality (yearly follow-up evaluations with mortality as an additional endpoint are planned depending on subsequent funding), and cost effectiveness (direct treatment costs: medication, hospitalisation and other costs over a period of one year).

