### Trial design

The trial will be conducted as a multicentre, open, observer-blinded, parallel groups (3 groups) randomized controlled trial (RCT). 'Observer-blinded' means that treatment evaluations will be conducted by blinded assessors. Further blinding is not possible, given the comparison of clearly identifiable group interventions with treatment as usual. All eligible type 2 diabetes patients within the age range of 65 to 85 years who give informed consent will be screened at the participating trial sites in the multicentre trial. All patients with minor depression or mild major depression (3 to 6 depression symptoms according to DSM-IV-TR criteria) will be included in the trial, provided that they meet the other inclusion and exclusion criteria. Patients included in the MIND-DIA trial will be randomized to one of the three treatment conditions: CBT, SH or TAU. In all groups patients will receive diabetological treatment as usual by their treating physicians during the trial. After 12 weeks of open-label therapy, both group interventions will be reduced to one session per month in the long-term phase of the trial (12 additional months). At the 12-month follow-up, all groups will be re-examined regarding the primary outcome variable and all secondary variables. A first analysis is planned after the end of the short-term phase of the RCT without the analyses of the parameters for depression and HRQoL. Therefore, this interim analysis will not influence the primary results or the conduct of the trial. For the first funding phase, the duration of the MIND-DIA trial is expected to be approximately 36 months. Recruitment of patients started in May 2009. The trial design is shown in figure 1.

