### Outcome measures

The primary outcome variable is HRQoL as measured by the Short Form-36 [32]: z-values will be obtained by z-transformation of the SF-36 Mental Component Summary score based on means and standard deviations of age- and gender-matched reference groups from the German general population. This transformation will be performed because it is known that in some respects HRQoL decreases differently with age for men and women. Because the level of depressive symptoms is already relatively low in patients with subthreshold depression compared with patients who have major depression (notwithstanding a comparably low HRQoL), the possibility for improvement is reduced ('bottom effect'). Hence, when one assesses the efficacy of an intervention in this specific group, it seems reasonable to analyse, in additional studies, other important variables, e.g. HRQoL, as the primary outcome variable and depressive symptoms as a secondary variable among others. Results of our own research demonstrated that HRQoL is extremely reduced among diabetes patients with depressive symptoms: Differences in SF-36 z-values were -1.4 for the physical and -1.9 for the mental component, a finding that indicates that a bottom effect is not to be expected in HRQoL.

Secondary outcome variables are: HRQoL (physical component as measured by the Physical Component Summary Score), reduction of depressive symptoms (Quick Inventory of Depressive Symptomatology-Clinician Rated, QIDS-C-16 [33]; Hamilton Depression Scale, HAMD [34]), prevention of moderate/severe major depression (Depression module, SCID), improvement of glycaemic control (HbA1_c_), prevention of mortality, and cost-effectiveness. Standardised rater training of evaluators who were blind to treatment conditions was carried out for observer-derived depression assessments (QIDS-C, HAMD, SCID).

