#### Analysis of outcome variables

There will be one analysis of depression and health related quality of life after completion of the trial, i.e. no interim analyses are planned for the primary parameters. The primary response variable is the z-transformed SF-36 Mental Component Summary (MCS) score at the one-year follow-up. We plan to employ a linear regression model of z-transformed SF-36 score on type of intervention and baseline score. Additional variables (e.g. gender, age, centre, and illness severity) may be included in the model, if indicated.

The hypotheses will be ordered hierarchically (1: CBT vs. TAU, 2: CBT vs. SH); the second hypothesis will be tested at a two-sided 5% level only if the first test is significant at a two-sided 5% level. Analyses will be performed using an intent-to-treat analysis, and the last observation carried forward method will be used for the handling of missing data. Secondary outcomes (HRQoL (physical component), severity of depression, prophylaxis of moderate/severe major depression, glycaemic control (HbA1c), and mortality) will be analysed primarily in a descriptive manner. For binary response variables, the numbers and proportion of responders will be presented together with 95% confidence intervals for the proportions; continuous variables will be analysed by use of summary statistics. If differences between intervention groups are investigated, outcomes will be adjusted for baseline values through use of appropriate models (linear, logistic, or Poisson regression); however, the p-values for such secondary analyses may not be interpreted as confirmatory findings. Subgroup analyses stratified for gender (male/female), mild cognitive impairment (yes/no), and number of previous depressive episodes (<3, ≥3) also will be carried out. These analyses will be conducted using the same methods as those for the full population. Time to onset of moderate/severe major depression and conversion rates to dementia will be analysed using Kaplan-Maier estimates.

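### The hypothesis that CBT beats TAU on depressive symptoms has no confirmatory test, and no blinded-rater outcome is in the confirmatory family; a gated third step would add both without cost to the first two tests

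*Protocol article*

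**What the plan says.** Under Trial objectives and endpoints, the protocol article puts two kinds of claim among the secondary hypotheses. One is that CBT improves health-related quality of life more than SH. The other is a list of CBT vs TAU claims at one year, which begins: "CBT will be found to be significantly more effective than TAU in terms of reduction of depressive symptoms".

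Under Analysis of outcome variables, the primary response is the z-transformed SF-36 MCS at the one-year follow-up. The confirmatory family is stated as follows: "The hypotheses will be ordered hierarchically (1: CBT vs. TAU, 2: CBT vs. SH"), and "the second hypothesis will be tested at a two-sided 5% level only if the first test is significant at a two-sided 5% level". Secondary outcomes, with severity of depression among them, "will be analysed primarily in a descriptive manner". Group comparisons are permitted: "If differences between intervention groups are investigated, outcomes will be adjusted for baseline values through use of appropriate models". Their standing is then limited: "however, the p-values for such secondary analyses may not be interpreted as confirmatory findings".

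On blinding, Trial design calls the study open and explains the label: "Observer-blinded' means that treatment evaluations will be conducted by blinded assessors". It adds that no further blinding is possible. Outcome measures names the ratings made by blinded evaluators: "Standardised rater training of evaluators who were blind to treatment conditions was carried out for observer-derived depression assessments (QIDS-C, HAMD, SCID").

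**The concern.** The depression hypothesis is written in the language of significance, yet no test in the plan can establish it. The two kinds of secondary hypothesis are also treated differently: CBT vs SH on quality of life is step 2 of the hierarchy, while CBT vs TAU on depression is exploratory.

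The assessor blinding that gives the design its label is described for the depression ratings, and these lie outside the hierarchy. Both confirmatory tests use the MCS in patients who know their treatment. The first compares a group programme of 12 weekly and then monthly sessions with feedback plus any usual option, watchful waiting included. Differences in expectation and attention are likely to be largest there.

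At stake is what a positive trial may conclude. Depressive symptoms define eligibility, and the CBT programme is aimed at depression. If both planned tests succeed, the trial will still have no confirmatory result on depression and none produced by a blinded rater.

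**Working it through.** **1. The sections side by side**

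| Item | Trial objectives and endpoints | Analysis of outcome variables |
|---|---|---|
| CBT vs TAU, quality of life | primary hypothesis | step 1, two-sided 5% |
| CBT vs SH, quality of life | secondary hypothesis | step 2, two-sided 5%, gated |
| CBT vs TAU, depressive symptoms | secondary hypothesis, significant superiority expected | descriptive; p-values not confirmatory |

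**2. The plan's own power figures**

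Inputs from Sample size calculation: δ = 0.6 (CBT vs TAU), δ = 0.4 (CBT vs SH), groups of 132, 132 and 51, two-sided α = 0.05. I take the SD of the z-score as 1.

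Formula: power ≈ Φ(d/SE − 1.96), with SE = √(1/n₁ + 1/n₂).

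- CBT vs SH: SE = √(1/132 + 1/132) = 0.123; 0.4/0.123 − 1.96 = 1.29; power 90.1% (exact t: 89.9%). Stated: 90%.
- CBT vs TAU: SE = √(1/132 + 1/51) = 0.165; 0.6/0.165 − 1.96 = 1.68; power 95.3% (exact t: 95.2%). Stated: 95%.

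Both figures reproduce. Nothing in the sample size section is put in doubt by this point.

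**3. Error rate with a third step**

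In a fixed sequence, a false rejection requires rejecting the first true null hypothesis in the order. That has probability at most 5%, however many steps follow. Appending a step therefore keeps the familywise error at 5% and does not alter the level or power of steps 1 and 2.

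Testing without gating would be different. Five independent secondary tests at 5% each would give 1 − 0.95⁵ = 22.6%. Withholding confirmatory status from ungated secondary p-values is therefore sound.

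**4. Power of a third step, CBT vs TAU on a depression score**

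The article gives no effect size for depression, so the standardised difference d is assumed over a range. The planned 20% loss leaves 0.8 × 132 ≈ 106 and 0.8 × 51 ≈ 41. The plan carries the last observation forward, so the analysed numbers stay nominally at 132 and 51. The reduced numbers approximate the information actually collected at the final visit.

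Stand-alone power is from the exact t-test without gain from baseline adjustment. Power to pass all three steps is from a simulation of 40,000 runs. It uses the plan's MCS differences and an assumed correlation of 0.3 to 0.7 between MCS and depression score.

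| d | Stand-alone, 132 vs 51 | Stand-alone, 106 vs 41 | All three steps, full n | All three steps, 20% loss |
|---|---|---|---|---|
| 0.3 | 44% | 37% | not simulated | not simulated |
| 0.4 | 67% | 58% | 61–63% | 47–51% |
| 0.5 | 85% | 77% | 76–78% | 62–65% |
| 0.6 | 95% | 90% | 83–84% | 71–73% |

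At 132 vs 51 the normal approximation gives 68%, 86% and 95% for d = 0.4, 0.5 and 0.6, at most about one point higher. Stand-alone power reaches 80% at d = 0.46 with full numbers and at d = 0.52 after loss. Under the plan's own MCS assumptions, steps 1 and 2 both succeed in about 87% of runs with full numbers and about 77% after loss, so step 3 would be reached that often.

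**The case against.** The strongest reply is that nothing here is wrong. The depression claim is labelled secondary, the hierarchy is stated openly, and all other outcomes are treated alike as exploratory. That is a normal and valid plan, and this part of the reply stands in full.

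The article also explains its choice. Under Outcome measures it argues that patients with few symptoms have little room to improve on a depression scale, whereas their mental quality of life is markedly reduced. This justifies making quality of life primary. It does not justify keeping depression out of a later gated step, which cannot harm the earlier tests. It does make the smaller values of d, and so the lower powers, more relevant.

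On attention and expectation, CBT vs SH compares two group programmes, and SH was included to control for unspecific group effects. That weakens the concern about step 1. It does not remove it, since patients in both groups still know what they receive.

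The proposed step also has a limit: if CBT vs SH fails, step 3 is never reached and no confirmatory blinded result against TAU exists.

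A reader might infer two stronger points that the documents do not support:

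- That no depression claim of any kind can be made. The plan excludes only a confirmatory one. Baseline-adjusted comparisons of the blinded ratings may be made, reported and interpreted as exploratory.
- That the primary outcome is stated to be unblinded self-report. The article does not say who completes the SF-36. Self-report is an inference from the open design and from the SF-36 not being named among the observer-derived measures.

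**Conclusion.** The point holds as a mismatch between two sections and as an avoidable limitation. The significance wording of the depression hypothesis does not fit the exploratory status given to its analysis. As written, the chance of a confirmatory depression result is zero, and no outcome rated by the named blinded assessors is in the confirmatory family.

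No figure in the plan is wrong, and its multiplicity rule is valid. What could be gained depends on an effect size that the article does not give. After the planned loss, the chance of passing all three steps is about 47–51% at d = 0.4 and 71–73% at d = 0.6. These values rest on the plan's MCS differences being true, an SD of 1, the assumed correlation, and 106 vs 41 standing in for the effect of dropout. The change is worth making because it costs the first two tests nothing.

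**What to change.** In Analysis of outcome variables, extend the hierarchy with a third step: CBT vs TAU on one pre-named blinded-rater depression score (for example the HAMD total), at the same final visit as the primary outcome, adjusted for baseline, two-sided 5%, tested only if steps 1 and 2 are both significant. The article does not rank HAMD and QIDS-C, so the choice must be fixed before the data are seen; the other score is then supportive. State the power of this step with its assumed effect size and with the 20% loss.

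In Trial objectives and endpoints, word the remaining secondary hypotheses outside the hierarchy as exploratory aims. If the sponsor prefers not to add a third step, the depression hypothesis should be reworded in the same way. That removes the mismatch but leaves the limitation.

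The cost is a sentence or two in the protocol or analysis plan. Table 1 already schedules the QIDS/Hamilton ratings at baseline and months 3, 12 and 15, so no new data are needed.

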#### Safety

Differences between the treatment groups regarding rates of mortality and suicidality will be described descriptively. P-values from Fisher's exact test for pairwise comparison may be calculated but not interpreted in a confirmatory manner.

#### Ethical aspects

The procedures set out in the trial protocol regarding the conduct, evaluation, and documentation of this trial are designed to ensure that all persons involved in the trial abide by Good Clinical Practice (GCP) and the ethical principles described in the current revision of the Declaration of Helsinki. Clinical monitoring, data management, and biometry according to GCP will be conducted by IZKS Mainz. The trial will be carried out in keeping with local legal and regulatory requirements. All patients will be in treatment, regularly seen by diabetologists and trial clinicians. Before being admitted to the clinical trial, the patients must agree to participate after the nature, scope, and possibleconsequences of the trial have been explained in a form understandable to them. The patients must give written informed consent. A copy of the signed consent document must be given to each patient. The documents must be in language that is understandable to the patients and must specify who informed them. During the trial, patients will be identified solely by means of year of birth and an individual identification code (patient number, randomisation number). For protection of these data, organisational procedures will be implemented to prevent distribution of the data to unauthorised persons. The appropriate regulations of local data legislation will be followed in their entirety. Five independent ethics committees voted their approval of these procedures. The main ethics committee for the MIND-DIA trial is the local Medical Ethics Committee (Ethikkommission bei der Landesärztekammer Hessen); approval has been given on 09/04/2009. Further ethic committees which approved the MIND-DIA trail are: the local Medical Ethics Committee (Ethikkommission der Ärztekammer Nordrhein), the local Medical Ethics Committee (Ethikkommission der Ärztekammer Westfalen-Lippe) and the Ethics Committees of the Ruhr-University Bochum and the Johann-Wolfgang Goethe University, Frankfurt.
